## **2.0 OBJECTIVES**

### **2.1 Primary objective**

Phase II: To evaluate and compare the cCR rates in patients with locally advanced rectal cancer treated with neoadjuvant LCRT followed by neoadjuvant mFOLFIRINOX versus neoadjuvant LCRT followed by neoadjuvant mFOLFOX6.

Phase III: To evaluate and compare disease-free survival (DFS) in patients with locally advanced rectal cancer treated with neoadjuvant LCRT followed by neoadjuvant mFOLFIRINOX versus neoadjuvant LCRT followed by neoadjuvant mFOLFOX6.

### **2.2 Secondary objective(s)**

**2.2.1** To evaluate and compare organ-preservation-time (OPT) between two treatment arms.

**2.2.2** To evaluate and compare time to distant metastasis between two treatment arms.

**2.2.3** To evaluate and compare overall survival (OS) between two treatment arms.

**2.2.4** To evaluate and compare toxicity profiles of TNT between two treatment arms.

### **2.3 Exploratory objective**

**2.3.1** Evaluation of ctDNA kinetics during neoadjuvant therapy & surveillance and to correlate with radiographic, pathologic, and clinical outcomes.

### 3.0 PATIENT SELECTION

For questions regarding eligibility criteria, see the Study Resources page. Please note that the Study Chair cannot grant waivers to eligibility requirements.

#### 3.1 On-Study Guidelines

This clinical trial can fulfill its objectives only if patients appropriate for this trial are enrolled. All relevant medical and other considerations should be taken into account when deciding whether this protocol is appropriate for a particular patient. Physicians should consider the risks and benefits of any therapy, and therefore only enroll patients for whom this treatment is appropriate.

- Physicians should consider whether any medical conditions would make this protocol unreasonably hazardous for the patient.
- Patients with a prior or concurrent malignancy whose natural history or treatment does not have the potential to interfere with the safety or efficacy assessment of the investigational neoadjuvant regimen or primary endpoint are eligible for this trial.

In addition:

- Women and men of reproductive potential should agree to use an appropriate method of birth control throughout their participation in this study due to the teratogenic potential of the therapy utilized in this trial. Appropriate methods of birth control include abstinence, oral contraceptives, implantable hormonal contraceptives or double barrier method (diaphragm plus condom).

#### 3.2 Eligibility Criteria

Use the spaces provided to confirm a patient's eligibility by indicating Yes or No as appropriate. It is not required to complete or submit the following page(s).

When calculating days of tests and measurements, the day a test or measurement is done is considered Day 0. Therefore, if a test were done on a Monday, the Monday one week later would be considered Day 7.

A female of childbearing potential is a sexually mature female who: 1) has not undergone a hysterectomy or bilateral oophorectomy; or 2) has not been naturally postmenopausal for at least 12 consecutive months (i.e., has had menses at any time in the preceding 12 consecutive months).

##### 3.2.1 Documentation of Disease

###### Histologic Documentation:

**Stage:** Clinical stage II or III rectal adenocarcinoma defined as T4N0 or any T with node positive disease (any T, N+); also T3N0 requiring APR or coloanal anastomosis

**Tumor Site:** Rectum;  $\leq 12$ cm from the anal verge

##### 3.2.2 Prior Treatment

No prior systemic chemotherapy, targeted therapy, or immunotherapy; or radiation therapy administered as treatment for colorectal cancer within the past 5 years is allowed.

— **3.2.3 Not pregnant and not nursing**, because this study involves an agent that has known genotoxic, mutagenic and teratogenic effects.

Therefore, for women of childbearing potential only, a negative pregnancy test (urine or serum according to institutional guidelines) done  $\leq 14$  days prior to registration is required. Female subjects agree to use highly effective contraception combined with an additional barrier method (eg, diaphragm, with a spermicide) while on study and for  $\geq 9$  months after last dose of study drug, and the same criteria are applicable to male subjects if they have a partner of childbirth potential. Male subject agrees to use a condom and not donate sperm while in this study and for  $\geq 6$  months after the last treatment.

— **3.2.4 Age  $\geq 18$  years**

— **3.2.5 ECOG Performance Status 0-1 (or Karnofsky  $\geq 60\%$ )**

— **3.2.6 Required Initial Laboratory Values:**

|                                 |                                                  |
|---------------------------------|--------------------------------------------------|
| Absolute Neutrophil Count (ANC) | $\geq 1,500/\text{mm}^3$                         |
| Platelet Count                  | $\geq 100,000/\text{mm}^3$                       |
| Creatinine                      | $\leq 1.5 \times$ upper limit of normal (ULN) OR |
| Calc. Creatinine Clearance      | $\geq 50 \text{ mL/min}$                         |
| Total Bilirubin                 | $\leq 1.5 \times$ upper limit of normal (ULN)    |
| AST / ALT                       | $\leq 3 \times$ upper limit of normal (ULN)      |

— **3.2.7 Comorbid conditions**

- No upper rectal tumors (distal margin of tumor  $>12$  cm from the anal verge)
- No recurrent rectal cancer; prior transanal excision, prior distal sigmoid cancer with a low anastomosis
- No known mismatch repair deficient rectal adenocarcinoma
- HIV-infected patients on effective anti-retroviral therapy with undetectable viral load within 6 months are eligible for this trial.
- Patients with known history or current symptoms of cardiac disease, or history of treatment with cardiotoxic agents, should have a clinical risk assessment of cardiac function using the New York Heart Association Functional Classification. To be eligible for this trial, patients should be class 2B or better.

— **3.2.8 Concomitant medications**

Chronic concomitant treatment with strong inhibitors of CYP3A4 is not allowed on this study. Patients on strong CYP3A4 inhibitors must discontinue the drug for 14 days prior to registration on the study.

Chronic concomitant treatment with strong CYP3A4 inducers is not allowed. Patients must discontinue the drug 14 days prior to the start of study treatment.

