**Eligibility Criteria (see Section 3.2)**

- Clinical stage II or III rectal adenocarcinoma defined as T4N0, or any T with node positive disease (any T, N+); also T3N0 requiring APR or coloanal anastomosis
- No prior systemic chemotherapy, targeted therapy, or immunotherapy; or radiation therapy administered as treatment for colorectal cancer within the past 5 years
- Not pregnant and not nursing
- Age  $\geq 18$  years
- ECOG Performance Status 0-1
- No upper rectal tumors (distal margin of tumor  $> 12$  cm from the anal verge)
- No recurrent rectal cancer; prior transanal excision, prior distal sigmoid cancer with a low anastomosis
- No known mismatch repair deficient rectal adenocarcinoma

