**Please refer to the full protocol text for a complete description of the eligibility criteria and treatment plan.**

If the Group credited for enrollment is a non-Alliance Group, then other requirements from the credited Group may apply.

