##### 4.5.2 Treatment Assignments

The factors defined in Section 4.5.1 will be used as stratification factors.

After the patient has been registered into the study, the values of the stratification factors will be recorded, and the patient will be assigned to one of the following treatment groups using the Pocock and Simon dynamic allocation procedure which balances the marginal distributions of the stratification factors between the treatment groups.

- 1) LCRT followed by mFOLFOX6 (or CAPOX)
- 2) LCRT followed by mFOLFIRINOX

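### Section 3.2.5 offers Karnofsky 60% or higher as an alternative to ECOG 0-1; on the usual crosswalk the two are not equivalent, and the eligibility summary gives only ECOG 0-1

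*Combined protocol and SAP*

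**What the plan says.** Performance status appears as an entry condition in two places.

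- The eligibility summary before the schema states "ECOG Performance Status 0-1" and nothing more on the subject. Its heading, "Eligibility Criteria (see Section 3.2", points to the full section.
- Section 3.2.5 states "ECOG Performance Status 0-1 (or Karnofsky" and completes the parenthesis with a threshold of 60% or higher.

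Three other provisions settle how these are used. The note after the schema says: "Please refer to the full protocol text for a complete description of the eligibility criteria and treatment plan". The opening of Section 3.0 says that "the Study Chair cannot grant waivers to eligibility requirements". Section 4.4 tells sites to confirm that all eligibility criteria are met before they open the enrollment system.

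The footnote to the Arm 1 and Arm 2 calendars in Section 5.0 requires performance status before treatment, at week 10 and at weeks 32-38. It does not say which scale to record.

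**The concern.** A parenthesis beginning with 'or' normally offers either an equivalent or a second way to qualify. If Karnofsky 60 were equivalent to the bottom of ECOG 1, the wording would be harmless and the summary merely shorter. If Karnofsky 60 lies below ECOG 1, the criterion contradicts itself: its first half excludes a patient whom its second half admits.

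What is at stake is the definition of the trial population. Without waivers, the written words decide who enters, and here they allow two answers for the same patient. Section 12.5 defines an ineligible patient as one who does not meet every criterion. Section 13.4.1 restricts the per-protocol population to patients deemed eligible, and Section 13.4.2 uses that population for sensitivity analyses in both phases. An eligibility rule with two readings makes that population harder to define consistently. It also leaves open whether the trial can be described, without qualification, as one in ECOG 0-1 patients.

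**Working it through.** No plan figure needs reproducing, since the point involves no sample size, power, alpha or event count. The check is a comparison of texts.

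**Step 1: which text governs.** The summary refers to Section 3.2, and the note after the schema sends the reader to the full text. Section 3.2.5 is therefore operative, and its Karnofsky alternative counts.

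**Step 2: whether anything else limits that alternative.** No other section defines either scale, gives a conversion, says which scale prevails when they disagree, or narrows the Karnofsky route.

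**Step 3: apply each wording to the same patient.** The conversion is an assumption. The usual crosswalks agree that Karnofsky 60 is ECOG 2 but differ on whether Karnofsky 70 is ECOG 1 or ECOG 2, so both versions are shown.

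| Patient | ECOG half of 3.2.5 | Karnofsky half of 3.2.5 | 3.2.5 as written | Summary |
|---|---|---|---|---|
| Karnofsky 60, taken as ECOG 2 | not met | met | eligible | not eligible |
| Karnofsky 70, if taken as ECOG 1 | met | met | eligible | eligible |
| Karnofsky 70, if taken as ECOG 2 | not met | met | eligible | not eligible |

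The mismatch covers Karnofsky 60 on either version, and Karnofsky 60 and 70 on the version that puts 70 at ECOG 2. The first row shows that the two halves of 3.2.5 disagree with each other even if the summary is set aside.

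**Step 4: which patients and arms are affected.** Section 4.5.2 assigns every registered patient either to the doublet (mFOLFOX6 or CAPOX) or to "LCRT followed by mFOLFIRINOX", and Section 13.3 makes the ratio 1:1. Anyone entering by the Karnofsky route can go to either arm. Performance status is not a stratification factor in Section 4.5.1, but allocation does not depend on which half of the criterion was met.

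**Step 5: size.** A count would need the share of registered patients at Karnofsky 60 (or 60-70). The documents give no such share and nothing from which to derive one, so no number of patients out of the planned 760 can be supported.

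**The case against.** The strongest reply has four parts.

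1. *The summary is an abridgement.* It defers to Section 3.2 and also leaves out the HIV, cardiac-class and CYP3A4 conditions. This stands: the summary is not a rival rule. But leaving out further restrictions makes a summary look looser than the full text, whereas leaving out this alternative makes it look stricter. The conflict inside 3.2.5 does not depend on the summary at all.

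2. *The conversion is not in the documents.* This also stands, which is why it is labelled an assumption. From the documents alone, one can say only that 3.2.5 contains an alternative that the summary omits and that its equivalence to ECOG 0-1 is nowhere shown.

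3. *The parenthesis may have been meant as a conversion of ECOG 0-1, not a second route.* The text allows that reading. On the assumed crosswalk the stated conversion would then be wrong, and the wording would still need correcting.

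4. *There are safeguards.* Section 3.1 asks physicians to enroll only patients for whom the treatment is appropriate, and Section 13.5.1 monitors early discontinuation and grade 4 or higher toxicity. These reduce the practical risk but do not define the entry limit.

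A reader might also infer more than the documents support:

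- *That the triplet arm receives frailer patients, or that the comparison is biased.* Randomization applies equally to everyone who enters.
- *That entry depends on which scale a site uses.* As written, the alternative is open to every site.
- *That toxicity or early discontinuation will rise, or that the safety rules or the phase II analysis population will be disturbed.* Frailer patients may tolerate treatment less well, but the documents give no figure from which to judge the effect.
- *That the result could never be reported for ECOG 0-1 patients.* Performance status is collected at baseline, so the enrolled population can be described, provided the recorded scale permits it.

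**Conclusion.** The inconsistency is real and sits in an operative entry criterion. On the assumption that Karnofsky 60 corresponds to ECOG 2, Section 3.2.5 as written can admit patients to either arm whom its own ECOG 0-1 limit, and the eligibility summary, would exclude. The gap is at least Karnofsky 60, and it reaches Karnofsky 70 on some versions of the crosswalk.

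Confidence is high that the two wordings differ. That they admit different patients rests on the crosswalk. The number of patients affected is unknown and could be zero. The definitions of the intent-to-treat population (phase III primary analysis) and the modified intent-to-treat population (phase II primary analysis) do not refer to an eligibility ruling. The per-protocol definition does, so the sensitivity analyses are where the ambiguity could enter directly.

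A reader might infer that the stricter limit must be the intended one. The documents do not show that: the summary's own deference to Section 3.2 points to the wider text, while the ECOG half of 3.2.5 points to the narrower one. Which limit is right is for the study team to decide.

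**What to change.** Reconcile the eligibility summary and Section 3.2.5 by amendment:

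1. The study team decides and states the intended performance-status limit.
2. It either removes the Karnofsky alternative or sets it to the value equivalent to the stated ECOG range, giving the conversion relied on.
3. Identical wording goes into the summary, Section 3.2.5 and the registration checklist. That checklist is not among the documents reviewed, so its present wording should be checked first.
4. The Section 5.0 footnote names the scale to be recorded at baseline.

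The cost is a one-line change to the criterion with matching edits to the summary, checklist and footnote. If the team chooses the narrower limit, a few patients who now qualify by Karnofsky score may be excluded. No sample size, boundary or analysis method needs to change.

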## 4.0 PATIENT REGISTRATION

### 4.1 Investigator and Research Associate registration with CTEP

Food and Drug Administration (FDA) regulations require sponsors to select qualified investigators. National Cancer Institute (NCI) policy requires all individuals contributing to NCI-sponsored trials to register with their qualifications and credentials and to renew their registration annually. To register, all individuals must obtain a Cancer Therapy Evaluation Program (CTEP) credentials necessary to access secure NCI Clinical Oncology Research Enterprise (CORE) systems. Investigators and clinical site staff who are significant contributors to research must register in the [Registration and Credential Repository](#) (RCR). The RCR is a self-service online person registration application with electronic signature and document submission capability.

RCR utilizes five person registration types.

- **Investigator (IVR)** — MD, DO, or international equivalent;
- **Non Physician Investigator (NPIVR)** — advanced practice providers (e.g., NP or PA) or graduate level researchers (e.g., PhD);
- **Associate Plus (AP)** — clinical site staff (e.g., RN or CRA) with data entry access to CTSU applications such as the Roster Update Management System (RUMS), OPEN, Rave; acting as a primary site contact, or with consenting privileges
- **Associate (A)** — other clinical site staff involved in the conduct of NCI-sponsored trials; and
- **Associate Basic (AB)** — individuals (e.g., pharmaceutical company employees) with limited access to NCI-supported systems.

RCR requires the following registration documents:

| Documentation Required                                                      | IVR | NPIVR | AP | A | AB |
|-----------------------------------------------------------------------------|-----|-------|----|---|----|
| FDA Form 1572                                                               | ✓   | ✓     |    |   |    |
| Financial Disclosure Form                                                   | ✓   | ✓     | ✓  |   |    |
| NCI Biosketch (education, training, employment, license, and certification) | ✓   | ✓     | ✓  |   |    |
| GCP training                                                                | ✓   | ✓     | ✓  |   |    |
| Agent Shipment Form (if applicable)                                         | ✓   |       |    |   |    |
| CV (optional)                                                               | ✓   | ✓     | ✓  |   |    |

In addition, IVRs and NPIVRs must list all clinical practice sites and Institutional Review Boards (IRBs) covering their practice sites on the FDA Form 1572 in RCR to allow the following:

- Addition to a site roster;
- Selection as the treating, credit, or drug shipment investigator or consenting person in OPEN;
- Ability to be named as the site-protocol Principal Investigator (PI) on the IRB approval; and
- Assignment of the Clinical Investigator (CI) task on the Delegation of Tasks Log (DTL).

In addition, all investigators acting as the Site-Protocol PI (investigator listed on the IRB approval), consenting/treating/drug shipment investigator in OPEN, or as the CI on the DTL must be rostered at the enrolling site with a participating organization.

Refer to the [NCI RCR](#) page on the [CTEP website](#) for additional information. For questions, please contact the **RCR Help Desk** by email at [[contact]](mailto:[contact]).

## 4.2 Cancer Trials Support Unit registration procedures

Permission to view and download this protocol and its supporting documents is restricted and is based on the person and site roster assignment housed in the Roster Maintenance application and in most cases viewable and manageable via the Roster Update Management System (RUMS) on the Cancer Trials Support Unit (CTSU) members' website.

This study is supported by the NCI CTSU.

### IRB Approval

As of March 1, 2019, all U.S.-based sites must be members of the NCI Central Institutional Review Board (NCI CIRB) in order to participate in Cancer Therapy Evaluation Program (CTEP) and Division of Cancer Prevention (DCP) studies open to the National Clinical Trials Network (NCTN) and NCI Community Oncology Research Program (NCORP) Research Bases. In addition, U.S.-based sites must accept the NCI CIRB review to activate new studies at the site after March 1, 2019. Local IRB review will continue to be accepted for studies that are not reviewed by the CIRB, or if the study was previously open at the site under the local IRB. International sites should continue to submit Research Ethics Board (REB) approval to the CTSU Regulatory Office following country-specific regulations.

Sites participating with the NCI CIRB must submit the Study Specific Worksheet (SSW) for Local Context to the CIRB using IRBManager to indicate their intent to open the study locally. The NCI CIRB's approval of the SSW is automatically communicated to the CTSU Regulatory Office, but sites are required to contact the CTSU Regulatory Office at [[contact]](mailto:[contact]) to establish site preferences for applying NCI CIRB approvals across their Signatory Network. Site preferences can be set at the network or protocol level. Questions about establishing site preferences can be addressed to the CTSU Regulatory Office by email or calling [name].

Sites using their local IRB or REB, must submit their approval to the CTSU Regulatory Office using the Regulatory Submission Portal located in the Regulatory section of the CTSU website. Acceptable documentation of local IRB/REB approval includes:

- Local IRB documentation;
- IRB-signed CTSU IRB Certification Form; and/or
- Protocol of Human Subjects Assurance Identification/IRB Certification/Declaration of Exemption Form.

In addition, the Site-Protocol Principal Investigator (PI) (i.e., the investigator on the IRB/REB approval) must meet the following criteria for the site to be able to have an Approved status following processing of the IRB/REB approval record:

- Have an Active CTEP status;
- Have an active status at the site(s) on the IRB/REB approval on at least one participating organization's roster;
- If using NCI CIRB, be active on the NCI CIRB roster under the applicable Signatory Institution(s) record;

- Include the IRB number of the IRB providing approval in the Form FDA 1572 in the RCR profile;
- List all sites on the IRB/REB approval as Practice Sites in the Form FDA 1572 in the RCR profile; and
- Have the appropriate CTEP registration type for the protocol.

#### **4.2.1 Additional site registration requirements**

Additional site requirements to obtain an approved site registration status include:

- An active Federal Wide Assurance (FWA) number;
- An active roster affiliation with the Lead Protocol Organization (LPO) or a Participating Organization (PO)
- An active roster affiliation with the NCI CIRB roster under at least one CIRB Signatory Institution (US sites only); and
- Compliance with all applicable protocol-specific requirements (PSRs).

#### **4.2.2 Protocol specific requirements for A022104 site registration**

##### **IROC credentialing:**

This is a study with a radiation and/or imaging (RTI) component and the enrolling site must be aligned to an RTI provider. To manage provider associations or to add or remove associated providers, access the Provider Association page from the Regulatory section on the CTSU members' website at <https://www.ctsu.org/RSS/RTFProviderAssociation>. Sites must be linked to at least one Imaging and Radiation Oncology Core (IROC) provider to participate on trials with an RTI component. Enrolling sites are responsible for ensuring that the appropriate agreements and IRB approvals are in place with their RTI provider. An individual with a primary role on a treating site roster can update the provider associations, though all individuals at a site may view provider associations. To find who holds primary roles at your site, view the Person Roster Browser under the RUMS section on the CTSU website.

IROC Credentialing Status Inquiry (CSI) Form – this form is submitted to IROC Houston to verify credentialing status or to begin a new modality credentialing process.

To complete protocol-specific credentialing the RTI provider or enrolling site should follow instructions in the protocol to submit documentation or other materials to the designated IROC Quality Assurance (QA) center. Upon the IROC QA center approving the RTI provider for the study modality, IROC will automatically send the approval to the Regulatory and Roster Maintenance applications to comply with the protocol specific requirement unless otherwise noted at the bottom of the IROC Credentialing Approval notification. IROC will continue to copy the provider and/or enrolling site on modality approvals.

Upon site registration approval in the Regulatory application, the enrolling site may access OPEN to complete enrollments. The enrolling site will select their credentialed provider treating the subject in the OPEN credentialing screen and may need to answer additional questions related to treatment in the eligibility checklist.

